# Effectiveness of wheelchair skills training for improving manual wheelchair mobility in children and adolescents: protocol for a multicenter randomized waitlist-controlled trial

**DOI:** 10.1186/s12887-023-04303-8

**Published:** 2023-09-26

**Keywords:** Children, Adolescents, Youth, Disability, Manual wheelchair, Wheelchair skills training, Participation

## Abstract

**Background:**

Self-directed mobility during childhood can influence development, social participation, and independent living later in life. For children who experience challenges with walking, manual wheelchairs (MWCs) provide a means for self-directed mobility. An effective MWC skills training program exists for adults, but controlled trials have not yet been documented in children and adolescents. This paper outlines the protocol for a multi-centre randomized wait-list controlled trial. The primary objective is to test the hypothesis that children and adolescents who receive MWC skills training will have higher MWC skills capacity compared to children and adolescents in the control group who receive usual care. The secondary objectives are to explore the influence of MWC skills training in children and adolescents (MWC use self-efficacy and satisfaction with participation in meaningful activities), and parents (perceived MWC skills); and to measure retention three months later.

**Methods:**

A multi-centre, parallel-group, single-blind randomized wait-list controlled trial will be conducted. A sample of 60 children and adolescents who use MWCs will be recruited in rehabilitation centres, specialized schools, and the communities of three Canadian cities. Participants will be randomized (1:1) to the experimental (Wheelchair Skills Training Program [WSTP]) or wait-list control group (usual care). Performance-based and self-report measures will be completed at baseline (T1), three months (post-intervention, T2), and three months post-intervention (T3). The primary outcome will be MWC skills capacity post-intervention. Secondary outcomes will be MWC use self-efficacy and satisfaction with participation of the child/adolescent, and parent-perceived MWC skills. The WSTP will consist of 12 sessions, 45–60 min each, delivered 1–2 times per week by trained personnel with health professions education. Training will be customized according to the child’s baseline skills and participation goals that require the use of the MWC. The wait-list control group will receive usual care for 3 months and then receive the WSTP after completing T2 evaluations. Data will be analysed using ANCOVA (controlling for baseline scores).

**Discussion:**

MWC skills training may be one way to improve self-directed mobility and related outcomes for children and adolescents. The results of this multi-centre randomized wait-list controlled trial will allow for the effectiveness of the intervention to be evaluated in a variety of clinical contexts and geographical regions.

**Trial registration:**

ClinicalTrials.gov: NCT05564247, Version October 3, 2022.

## Background

Self-directed mobility during childhood, defined as the ability to move in the manner and at the time of one’s own choice [1], is associated with attainment of developmental milestones, social participation, and increased likelihood of gainful employment and independent living in adulthood [2–4]. For children and adolescents who have trouble walking, manual wheelchairs (MWC) may be helpful. However, children and adolescents who use MWCs often rely on their parents and others for mobility, and thus may miss opportunities for participation, and play [5]. Moreover, they may have fewer opportunities to make choices and decisions about what they want to do and where they want to go, which may contribute to learned helplessness, restricted participation in physical activities, and social isolation [6–12]. Although self-directed mobility can contribute to child development and positively influence health-related quality of life and self-esteem [13–16], simply providing a MWC does not guarantee independent or safe use. The World Health Organization recommends a four-step approach to wheelchair service provision, one of which is training [1].

Improper MWC use can increase the risk of acute injuries due to accidents (e.g., tips, falls) and repetitive strain injuries [17, 18]. Between 1991 to 2008, approximately 44,300 American children and adolescents were treated in emergency departments for injuries related to using a wheelchair [19]. Furthermore, inadequate MWC skills can limit mobility and restrict participation, thus increasing risk of secondary chronic health conditions (e.g., cardiovascular disease, diabetes, obesity) [20]. In fact, MWC skills competence was highlighted as an important factor when aiming to improve participation in physical activity, which promotes health and quality of life [21].

Despite the importance of MWC skills, few children and adolescents receive adequate training to improve the skills needed for safe, self-directed mobility in the community and social participation. For example, in a survey of 68 Canadian rehabilitation centres (43 of which provided services to children), more than half reported that therapists trained MWC skills for two hours or less while 18% of centres reported therapists provided no training at all [22]. Similarly in one Canadian rehabilitation centre, 18 parents and child and adolescent MWC users affirmed receiving less than adequate MWC skills training [23]. In this study, 64% of occupational therapists from two specialized schools and a rehabilitation centre for children and adolescents reported they provided MWC skills training, but only 4% did so as a part of their regular practice. In the total sample, 26% used a standardized program such as the Wheelchair Skills Training Program (WSTP), and 74% spent an average of 3 h or less on training [23]. In both studies, the key barriers to providing MWC skills training were lack of time, resources, and knowledge [22, 23].

The WSTP, the training component of the evidence-based Wheelchair Skills Program (WSP), may help to address training needs for children and adolescents, as it is safe and effective for improving MWC skills in various adult populations (e.g., wheelchair users, therapists, caregivers) and in a variety of rehabilitation and community settings [24, 25]. The evidence supporting the WSTP approach in children and adolescents is promising, with four single-group studies (total *n*= 28) showing statistically significant within-subject improvements in MWC skills after training [26–29]. Training with children and adolescents was conducted in clinical and community settings, including as part of regular physical education classes during the academic year [27], and during two condensed 2–4 h sessions [26, 28]. Parents also perceived that their child had increased independence, improved MWC skills, and decreased shoulder pain after completing the WSP [26, 28]. However, to date no randomized controlled trials have been documented in children and adolescents.

This paper outlines the protocol of a randomized wait-list controlled trial which aims to document the influence of the WSTP on MWC skills and mobility outcomes in children and adolescents. The primary objective is to test the hypothesis that children and adolescents who receive the WSTP will have higher MWC skills capacity compared to children and adolescents in the control group who receive usual care. The secondary objectives are to explore: 1) the effects of the WSTP on MWC activity, MWC use self-efficacy and satisfaction with participation in meaningful activities among children and adolescents; 2) the influence of the WSTP on parent-perceived MWC skills capacity and performance and satisfaction with participation; and 3) retention of all primary and secondary outcomes among children, adolescents, and parents 3-months post-intervention.

## Methods

### Design

A multi-site, parallel-groups, single-blind (testers) randomized wait-list controlled trial will be conducted in three Canadian cities (Quebec City, Montreal, Halifax). Participants will be randomly assigned to the experimental group (WSTP) or the control group (usual care) using a 1:1 allocation ratio between groups. A computerized randomization process, stratified by site (3 sites) and age (categorized according to the National Institute of Child Health and Human Development, which defines childhood as 2 to 11 years and adolescence as 12 to 18 years of age [30]) with undisclosed block sizes will be conducted by a research professional who is not involved in the study, and the allocation sequence will be placed in sealed opaque envelopes. A trial coordinator at the primary site (Quebec City) who is not involved in any other aspect of the research will manage randomization for all sites. The site coordinator will email the trial coordinator after completion of T_1_ assessments, and the trial coordinator will open the sealed envelope and reply with participant allocation within 24 hours. A site coordinator at each site will communicate with the trial coordinator and will manage recruitment, enrollment, and participant flow through the study.

### Participants and recruitment

To be included in this study, children and adolescents will be between the ages of 4 to 18 years (based on the National Institute of Child Health and Human Development definition [30] and education and rehabilitation services in Eastern Canada); have a MWC for mobility purposes; be able to self-propel a MWC for at least 10 m; be willing to participate in the study (create participation goals at baseline); be able to indicate a need or answer a simple question (e.g., multiple choice) verbally or with a non-oral mode of communication (e.g., pictograms, communication devices); and be able to follow a two-step command evaluated in one of two ways: 1) the parent or guardian who completes eligibility screening is asked by the research coordinator whether their child can follow a two-step command or 2) the clinician involved in recruitment is asked by the research coordinator whether their child can follow a two-step command. Exclusion criteria include children who use a MWC with double hand-rim (as the WSTP does not currently include specific training instructions), an anticipated health condition or procedure that could contraindicate training or testing in the next six months (e.g., surgery); and a degenerative condition that is expected to progress quickly.

Convenience sampling will be used to recruit 60 children and adolescents (targeting 20 per site), a sample size based on a power analysis (described below). Active recruitment strategies will include working with clinical collaborators to recruit in local rehabilitation centres and specialized schools in Quebec City (Centre intégré universitaire de santé et de services sociaux de la Capitale-Nationale (CIUSSS-CN), Madeleine Bergeron), Montreal (Marie-Enfant Rehabilitation Centre (CRME), Victor Doré, Joseph Charbonneau, Jean-Piaget) and Halifax (IWK Health Centre, Westmount). Clinicians from the pediatric rehabilitation centres at each site will discuss the study with families who may be eligible. Passive recruitment strategies will also include dissemination of promotional videos and posters on social media and websites of collaborators and community organizations.

### Procedures

Participants will complete baseline measures (T_1_) and then be assigned to the experimental or control group. The site coordinator will contact the trainer after T_1_ for participants assigned to the intervention group_._ Participants will be asked to attend 12 sessions of the WSTP intervention or continue to receive usual care (3 months), and then complete post-intervention outcomes (T_2_), ideally within a target of one to four days after training. All outcomes will be collected three months after T_2_ to assess retention of skills (T_3_). The site coordinator will schedule all assessments at T_1,_ T_2_ and T_3_ for both groups, as testers will remain blinded to group assignment throughout the study. The site coordinator will call participants 24–48 h in advance of testing and remind the participants about the importance of not revealing to the tester in which group they were assigned. Tester training will include watching an instructional video series (1 h, 37 min total) on how to complete the outcomes and customized in-person or virtual training depending on experience and needs. All data will be stored in a locked channel on Microsoft teams that will be only accessible to testers and the primary investigators. The trial design is depicted in Fig. 1.

**Fig. 1 Fig1:**
[figure not shown]
Trial design describing coordination, testing and experimental procedures

### Intervention (WSTP)

Participants allocated to the experimental group will complete a target of 12, 45–60 min sessions of the WSTP at a target frequency of 1 to 2 sessions per week. The WSTP will be delivered by trained personnel with education or experience in relevant fields (e.g., occupational therapy, physiotherapy, kinesiology, recreation therapy, adapted physical activity). Trainers may have various combinations of clinical practice or research experience with the WSTP. All trainers will complete self-directed WSTP training modules and hands-on practice until readiness to provide training is confirmed by [name], [name] or [name] (each have more than 20 years of experience in training individuals to administer the WSTP).

According to the WSP lesson plan [31], trainers will customize each session based on the age group (child or adolescent) and training goals of each child as determined during baseline testing and in the first training session. Goals can be adapted and modified over the course of the 12 weeks, which may increase motivation and adherence to the training protocol. Subsequent sessions will begin with a 5-min review of progress and socializing, followed by a 10-min warm-up (random practice of the previously learned skills); 20-min of attempting new skills (training on each skill will be carried forward to the next session until the skills are learned or until the trainer and participant mutually agree that training should be abandoned; the trainer will periodically ask the participant to practice newly learned skills to incorporate variability of practice); 10-min cool-down, during which the participant will practice skills in a self-determined manner.

The intervention will be delivered at university-affiliated health or research centres and the surrounding community (e.g., schools, homes, libraries, museums, parks) depending on preferred location and the child’s goals to enhance transferability of skills to real-life settings and to improve adherence to the intervention [31]. Fidelity of the WSTP administration will be evaluated by a member of the study team not involved in testing or training, who will watch one training session per participant (either in person or by video) randomly and at various times throughout the training period. The trainer will also complete a detailed training log and a checklist of standardized steps to be followed during training. Feedback and monthly discussions with trainers at each site will enhance fidelity. Any adverse events will be documented in the training logbook by the trainer. The logbook will also be used to document whether the participant requests to stop training or if they experience any health conditions that may impact or stop the training.

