### Wait-list control group

Children and adolescents in the control group will receive usual care during a 3-month period, which varies between and within regions [22]. During this time, participants will be considered on a waitlist to receive WSTP training and can continue or start any activities provided by therapists or in the community. After completion of T_2_ evaluations, children and adolescents in the control group will complete a target of 12, 45–60 min sessions of the WSTP, delivered by trained personnel as described for the experimental group.

Acknowledging that usual care may include some form of MWC skills training, previous evidence suggests the amount of training received during usual care according to the WSTP will be limited [22, 23].

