### Primary outcome

MWC skills capacity (i.e., what a person can do in a standardized environment) [32] will be assessed using the WST Version 5.3.1 for MWC users [31]. The child will be asked to execute 30 MWC skills in a standardized environment. Any adverse events during testing will be documented in the WST data collection form by the tester. Participants will be scored on a 4-point scale as Advanced pass (3), Pass (2), Partial pass (1), Fail (0), No part (NP), and Testing error (TE). The total percentage WST score is calculated as: Total percentage WST Capacity Score = sum of individual skill scores / ([# of possible skills – # of NP scores – # of TE scores] × 3) X 100%. As of February 8, 2023, there have been 112 studies indexed in PubMed about the WST (or the questionnaire version [WST-Q]) or that have used these as outcome measures [31]. A minimally clinical important difference (MCID) of 20% relative improvement in WST scores (T_1_ to T_2_) has been suggested for adults [24], but has not yet been determined for children.

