Enhancing self-directed mobility through MWC skills training may provide children with the dependent, indoor, community and advanced skills needed to use a MWC, thus could enhance participation in activities that require the use of a MWC (e.g., activities at school, sports, and active play), and reduce risks of acute (e.g., tips and falls) and overuse (e.g., repetitive strain due to poor propulsion techniques) injuries. Moreover, clinicians and community organizations have expressed interest in learning about MWC skills evaluation and training for integrating into clinical practice and community programs. For example, a community based physical activity organizing offering adapted physical activity programs would like to offer wheelchair skills training as a weekly program.

Establishing effect size in a randomized controlled trial will provide evidence to support integration of the WSTP into clinical and community partners to implement the WSTP as part of clinical practice and community-based program offering. Facilitators and barriers to using the WSTP may be explored with therapists and community partners. Implementation of the WSTP into regular clinical practice would ensure training starts early, specifically in fundamental skills (e.g., propulsion and maneuvering) and indoor skills required for getting around in the home and school. Extending MWC skills training into the community may reduce burden on rehabilitation therapists while responding to ongoing training needs as the child develops. For example, children receive new MWC as they grow. Approaches to performing community and advanced MWC skills, such as ascending curbs and steep ramp, may vary depending on MWC configuration and set-up. Moreover, having the opportunity to receive training when receiving a new MWC may enhance skills, safety and self-efficacy. In addition, if the child experiences a tip or fall, availability of wheelchair skills training in the community may provide an opportunity to rebuild skills and confidence on an as-needed basis. Future studies may consider implementation evaluation of the WSTP in clinical practice and ecological evaluations when training provided as a community-based program.

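### Between test visits, adverse events are recorded only through the trainer's logbook, so controls have no described capture from T1 to T2, nor the experimental arm from T2 to T3

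*Protocol article*

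**What the plan says.** The article describes two places where an adverse event is written down.

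- Intervention (WSTP): "Any adverse events will be documented in the training logbook by the trainer". The same logbook notes requests to stop training and whether participants have health problems: "if they experience any health conditions that may impact or stop the training".
- Primary outcome: "Any adverse events during testing will be documented in the WST data collection form by the tester". This form is used in both arms at T1, T2 and T3, and its scope is the test session.

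Whether a trainer is present depends on arm and period. Procedures: "The site coordinator will contact the trainer after T_1_ for participants assigned to the intervention group". Wait-list control group: "Children and adolescents in the control group will receive usual care during a 3-month period", during which they "can continue or start any activities provided by therapists or in the community". Only after the T2 assessment is it stated that "children and adolescents in the control group will complete a target of 12, 45–60 min sessions of the WSTP".

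No other section describes a question, diary or call about falls or injuries. This covers Procedures, Wait-list control group, Data collection methods, Secondary outcomes, Data management and Analyses. The coordinator's call shortly before each test is described only as a reminder to protect the tester's blinding.

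The Background links poor wheelchair use to tips, falls and repetitive strain. The Discussion says training could "reduce risks of acute (e.g., tips and falls) and overuse" injuries.

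**The concern.** From T1 to T2 one randomised arm is trained and the other is not. This is the only period in which a fair comparison of harms could be made. In that period the main recording route exists in one arm only, so the trained arm will tend to show more recorded events even if the true risk is equal.

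The direction of any true effect is open. Better skills could prevent tips and falls. Children who have just learned harder skills, and who are encouraged to use them in real settings, could also have more of them. As described, the data could neither support the expectation voiced in the Discussion nor reveal the opposite. A reader of the results who saw logbook events set out by arm could easily take a difference in recording for a difference in safety.

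**Working it through.** The plan states no event rate or harms figure, so there is nothing to reproduce. The check is a map of the described routes, followed by simple arithmetic.

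**Routes by arm and period**

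| Period | Experimental arm | Control arm |
|---|---|---|
| During the T1, T2 and T3 tests | Tester's form | Tester's form |
| Between T1 and T2 | Trainer's logbook | None described |
| Between T2 and T3 | None described | Trainer's logbook |

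The first row is balanced. The other two are not, and the imbalance reverses at T2.

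**Recording occasions**

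Inputs: 60 children in total (Sample size), 1:1 allocation (Design), target of 12 sessions each (Intervention; Wait-list control group).

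- Per arm: 60 / 2 = 30 children.
- T1 to T2: 30 × 12 = 360 target trainer contacts in the experimental arm, 0 in the control arm.
- T2 to T3: 0 described in the experimental arm, 30 × 12 = 360 in the control arm.

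**What unequal capture would do (illustration)**

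The documents give no event rate. Assume that the same share of each arm, 10% to 30%, truly has an event between the T1 and T2 tests, and that the logbook picks up 25% to 100% of affected children.

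Expected recorded = children × true share × capture.

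- Experimental arm, low end: 30 × 0.10 × 0.25 = 0.75 children.
- Experimental arm, middle: 30 × 0.20 × 0.50 = 3 children.
- Experimental arm, high end: 30 × 0.30 × 1.00 = 9 children.
- Control arm, in every case: 30 × share × 0 = 0 children.

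The true difference is zero throughout, so all of the recorded difference comes from capture.

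**How precise an even-handed comparison could be**

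Under the same assumed shares and full, equal capture, the half-width of an approximate 95% interval for the difference in proportions is 1.96 × √(2p(1 − p)/30).

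- p = 0.10: 1.96 × √(0.18/30) = 0.15.
- p = 0.20: 1.96 × √(0.32/30) = 0.20.
- p = 0.30: 1.96 × √(0.42/30) = 0.23.

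Even with equal capture, the comparison would be uncertain by about 15 to 23 percentage points either way.

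**The case against.** Four arguments count against the point.

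1. *The article is condensed.* Harms procedures are often left to the full protocol, and Fig. 1 is not shown. A wider procedure may exist. But the article does more than stay silent: it says who records events and where, and the imbalance follows from that mechanism combined with the trial design.

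2. *The logbook is not limited to events in sessions.* This stands. A reader might infer that events are recorded only during training sessions, that falls at home or school are missed in both arms, and that capture covers just the 9 to 12 hours of session time (12 × 45 min to 12 × 60 min). The text does not support this. The trainer's sentence covers any adverse event, whereas the tester's sentence is confined to testing. Health problems that affect training can arise anywhere. Later sessions open with a short review of progress, at which a family could mention a fall. What can be said is that such reports depend on someone volunteering them.

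3. *No comparison of harms is planned.* This also stands. Neither the objectives nor the Analyses section names a harms endpoint or a table by arm, and the Discussion sentence on injuries is hedged. The point is a limit on what the safety data can show, not an error in a stated analysis.

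4. *More recorded events in the trained arm is likely, not certain.* Agreed. The test form works in both arms and chance plays its part. The bias is a tendency, and after T2 it runs the other way.

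**Conclusion.** The point holds in this form. Apart from events during testing, the only described route is the trainer's logbook. It serves the experimental arm alone from T1 to T2 and, as described, the control arm alone from T2 to T3. Events outside sessions may reach the logbook, but nobody is described as asking for them in either arm. Recorded counts between tests would reflect contact with a trainer, about 360 target contacts against 0 in each period, rather than risk. The randomised period therefore could not show whether training raises or lowers tips, falls or injuries.

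This rests on the article as published, on full delivery of the target sessions and on about 30 children per arm. The range of 0.75 to 9 recorded children against 0 rests on assumed event and capture rates and only illustrates the mechanism. The primary outcome and its analysis are not touched. It is a moderate weakness in safety ascertainment that is worth repairing because the repair is cheap.

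**What to change.** At T2 and T3, ask the parent or child in both arms the same short question on tips, falls, injuries and upper-limb pain since the last visit. Put it in the parent REDCap form, which is already completed through a direct link, and do not collect it through the blinded tester. Word it without reference to training.

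Base any description of harms between arms on the T1–T2 answers alone, since only that period sets trained against untrained children as randomised. The T3 answers close the gap in the experimental arm after T2, but by then the controls are in training. Report logbook events separately, as events during training, and not as an arm comparison. If the full protocol already has such a procedure, state it in the article's place for adverse events.

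The cost is one item on an existing form at two visits. There are three downsides. Recall over three months is imperfect. Parents know the allocation and may notice or report events differently by arm. With about 30 children per arm the comparison is too imprecise for testing, so it should be presented as descriptive.
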